### 2.1. Design

The proposed study is a randomized controlled trial to assess the efficacy of a web-based parenting support program for promoting healthy eating and mealtime behaviours. There will be two data collection time-points: baseline and post-intervention (6 weeks after the intervention). All participants in the intervention group will receive the web-based Healthy Habits Triple P intervention. The control group, on the other hand, will only have access to the online intervention after completing the six-week follow-up assessment. All parents will receive a brochure on child nutrition, produced by the Australian government (National Health and Medical Research Council (2021)) [34].

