### 2.3. Sample Size

In this trial, following the recommendations of Whitehead et al. (2016), a sample size of 15 families per arm will be required with 90% power and two-sided 5% significance [35] and medium effect size (Cohen’s d = 0.5) based on meta-analysis of the effects of the Triple P on parenting and child outcomes [36]. Allowing for an attrition rate of 60%, 25 participants will be recruited to each arm. We have allowed for an attrition rate of 60%, which is greater than the traditional 20% attrition rate commonly used in trials of public health interventions. Participant anonymity in this study may contribute to reduced rates of assessment completion post-intervention [37]. An increase in sample size by 60% will ensure that sufficient sample size is retained.

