### 2.5. Randomisation, Allocation and Blinding

After the baseline survey is completed, participants will be randomly allocated to the intervention or the control groups in a 1:1 ratio using computer-generated block randomization schedule by a researcher not involved in data collection or recruitment, to facilitate equal group allocation. Because of the type of intervention used in this trial, participants cannot be blinded to group allocation.

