### 2.7. Data Collection

All data will be collected using validated parent-reported questionnaires that are to be completed online. Parents will complete the baseline survey soon after recruitment into the study and the post-intervention survey 6 weeks after randomization. Both the baseline and post-intervention surveys will be hosted on the Lime Survey platform. In order to minimize attrition, email reminders will be sent to parents to complete the modules and the post-intervention survey. The prompts will be sent out on a weekly basis after the participants are randomized. Additional reminders will be sent to families where post-intervention assessments have not been completed by the due date. The control group will complete the same set of assessments at the same time points.

Family socio-demographic information will be collected at baseline using the Family Background Questionnaire [40], including the child’s age, sex, postcode, the relationship of the respondent to the child, marital status, family structure, ethnicity, number of people living in the house, level of education, work status and country of birth of the respondent and their partner and the family’s ability to meet essential expenses.

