### 2.8. Primary Outcomes

The efficacy of the intervention will be measured through parent-reported changes in children’s diets using the validated Children’s Dietary Questionnaire (CDQ) [41]. The CDQ is a 28-item questionnaire that assesses children’s dietary intake patterns over the past week (or 24 h) for foods and beverages which are recommended or discouraged for health reasons. The tool was developed based on the Australian healthy eating guidelines and has demonstrated acceptable reliability and validity for assessing dietary patterns among preschool children at a population level [42]. It has been recommended for use in evaluating the efficacy of interventions to improve children’s eating habits [42]. All subscales of CDQ had Cronbach’s alpha (α) values of ≥0.6 [42].

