### 2.11. Quantitative Data Analysis

Quantitative data from this pilot study will be descriptive, with outcomes being interval estimates of variables relating to children’s dietary habits, parenting and child behaviours and parenting efficacy. Data will be de-identified, and SPSS (Version 27.0. Armonk, NY, USA: IBM Corp) will be used to conduct data analysis. Data will be examined for outliers and missing values. All data will be analyzed based on the intention to treat (ITT) principle. To account for repeated measurements, two-way repeated-measures ANOVAs will be used to evaluate changes in diet and other study outcomes between the intervention and control groups.

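### With one baseline and one follow-up, the planned repeated-measures ANOVA is a change-score t-test: valid, but usually less precise than adjusting the follow-up score for baseline

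*Protocol article*

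**What the plan says.** Section 2.1 fixes the number of assessments: "There will be two data collection time-points: baseline and post-intervention". Section 2.7 applies this to both arms: "The control group will complete the same set of assessments at the same time points". Section 2.5 places baseline before allocation: "After the baseline survey is completed, participants will be randomly allocated to the intervention or the control groups in a 1:1 ratio". Section 2.8 defines the primary outcome on the Children's Dietary Questionnaire (CDQ) in terms of change: "The efficacy of the intervention will be measured through parent-reported changes in children’s diets".

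Section 2.11 then names a single between-group method for diet and all other outcomes: "two-way repeated-measures ANOVAs will be used to evaluate changes in diet and other study outcomes between the intervention and control groups". It mentions no baseline covariate. The same section calls the study a pilot, describes the quantitative analysis as descriptive, and names interval estimates as its product.

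On size, section 2.3 states that "a sample size of 15 families per arm will be required with 90% power and two-sided 5% significance", with d = 0.5.

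**The concern.** A two-way (group by time) repeated-measures ANOVA sounds as though it draws on the correlation between visits. With only two visits, its group-by-time term compares mean change between arms and does nothing more. It subtracts the whole baseline score from each follow-up score, which amounts to fixing the baseline slope at 1. When the two visits have similar variances, the slope that the data support is the correlation between them, which is below 1.

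Two things are at stake:

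- **Interval width.** The intervals that section 2.11 names as the trial's output will usually be wider than the same data allow.
- **Chance imbalance.** With about 15 families per arm, sizeable baseline differences can arise by chance. A change score over-corrects for whatever difference occurs.

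**Working it through.** **Inputs.** Two assessments (2.1, 2.7); baseline before randomisation (2.5); two-sided 5%, d = 0.5, 15 per arm (2.3). Three further assumptions are needed: d is in units of the follow-up SD, variances are equal at the two visits, and the baseline-to-follow-up correlation ρ lies between 0.3 and about 0.9. The article gives no ρ for the CDQ. The only correlations it prints are test-retest values of 0.68 to 0.89 for the Parent and Toddler Feeding Assessment (PATFA), a secondary measure (2.9). They are a guide only, since retest is not six weeks under intervention.

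**The plan's own figure.** A two-arm comparison of means with d = 0.5, 90% power and two-sided 5% needs 2 × (1.96 + 1.2816)² / 0.5² = 84.1, so 85 per arm. Fifteen per arm gives 26% power (noncentral t). The stated 15 is not reproduced. That is a separate matter, and the present point does not depend on it.

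**Step 1: equivalence.** On a simulated data set with 15 per arm, the group-by-time F was 4.6516 and the squared t on change scores was 4.6516.

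**Step 2: variances.** In units of the outcome variance, per participant:

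- Change score: 2(1 − ρ).
- ANCOVA, large sample: 1 − ρ² = (1 − ρ)(1 + ρ).
- Ratio: (1 + ρ)/2.
- Estimating the slope in a small sample multiplies the ANCOVA variance by about 1 + 1/(2n − 4). This is 1 + 1/26 = 1.038 at n = 15 per arm and 1 + 1/16 = 1.063 at n = 10.

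**Step 3: power.** The noncentrality is 0.5 × √(n/(2V)), where V is the variance from step 2. The change score has 2n − 2 degrees of freedom and ANCOVA has 2n − 3. For example, at n = 15 and ρ = 0.5 the change score gives 0.5 × √(7.5/1.0) = 1.37. ANCOVA gives 0.5 × √(7.5/0.779) = 1.55.

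| ρ | Large-sample ratio | Ratio, 15 per arm | Power, 15 per arm: change → ANCOVA | Ratio, 10 per arm | Power, 10 per arm: change → ANCOVA |
|---|---|---|---|---|---|
| 0.3 | 0.65 | 0.68 | 20% → 27% | 0.69 | 14.6% → 18.9% |
| 0.5 | 0.75 | 0.78 | 26% → 32% | 0.80 | 18.5% → 21.9% |
| 0.7 | 0.85 | 0.88 | 40% → 44% | 0.90 | 27.7% → 30.0% |
| 0.89 | 0.945 | 0.98 | 80.5% → 81.1% | 1.004 | 61.6% → 61.2% |

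The 10-per-arm columns show what remains if 60% of the 25 recruited per arm are lost: 25 × 0.4 = 10.

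**Step 4: simulation check.** Ten thousand runs at 15 per arm gave variance ratios of 0.67, 0.78 and 0.89 at ρ = 0.3, 0.5 and 0.7. Both estimators averaged about 0.50, the true value.

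**Step 5: over-correction.** If the arms differ at baseline by D (in SD units), the expected change-score estimate is the true effect minus (1 − ρ)D, whereas ANCOVA's is the true effect. The standard deviation of D at 15 per arm is √(2/15) = 0.37. An imbalance of that size shifts the change-score estimate by 0.5 × 0.37 = 0.18 SD at ρ = 0.5, by 0.3 × 0.37 = 0.11 at ρ = 0.7 and by 0.11 × 0.37 = 0.04 at ρ = 0.89. The assumed effect is 0.5.

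**The case against.** The strongest reply is that this is a preference about efficiency and not an error. A repeated-measures ANOVA on randomised pre/post data is valid, and section 2.11 does not contradict itself here. The size of the gain rests on an assumed correlation. Across the printed PATFA range, the confidence interval at 15 per arm narrows by only about 6% (ρ = 0.68) to 1% (ρ = 0.89). The study is a descriptive pilot, and an analysis plan that is not shown might add a covariate. All of this limits the size of the point. It does not remove it, because the article itself names the model, and the model named is the less efficient one over most of the plausible range.

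Four stronger readings are tempting, and the documents do not support them:

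- **The planned analysis is biased.** Over randomisation it is not, as the simulated means show. The over-correction is conditional on a chance baseline difference.
- **Baseline adjustment can never be less precise.** That holds only in large samples. At 10 per arm and ρ = 0.89 the variance ratio is 1.004, slightly in favour of the change score.
- **The group main effect might be read as the treatment effect.** Section 2.11 speaks of changes compared between groups, and section 2.8 defines efficacy by change. Both point to the interaction.
- **The planned test is worse than ignoring baseline.** This would be so for ρ below 0.5, where 2(1 − ρ) exceeds 1. No figure in the article places ρ there.

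**Conclusion.** The point holds as an avoidable loss of precision, not as a threat to validity. The algebra is certain: with two time points the group-by-time test is the change-score test, and the large-sample variance ratio is (1 + ρ)/2.

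The practical size is less certain, because ρ is unknown for the CDQ. At 15 per arm the variance falls by roughly a third at ρ = 0.3, a fifth at 0.5, an eighth at 0.7 and almost nothing at 0.89. Power rises by 7, 6, 4 and about 1 percentage points. At about 10 per arm with ρ near 0.9 there is no gain.

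A reader might infer that changing the model would repair the power of the trial. It would not. For 90% power at d = 0.5, ANCOVA needs 64 per arm at ρ = 0.5 and 43 at ρ = 0.7, against 85 and 51 for the change score. Fifteen per arm would suffice only at ρ of about 0.91, under either analysis.

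The change should still be made. It costs almost nothing, and the intervals are what section 2.11 says the trial will deliver.

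**What to change.** In section 2.11, replace the two-way repeated-measures ANOVA with the following. For each outcome, compare the 6-week score between arms by ANCOVA, with arm and the baseline score of the same measure as the model terms (or use a baseline-constrained mixed model). Report the adjusted mean difference with its 95% confidence interval.

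This is a wording change. It needs no new data, because both arms already complete the same measures at baseline, and the named software can fit the model. The cost is one degree of freedom per analysis. It would also help to report the observed baseline-to-follow-up correlation for each outcome, since a later definitive trial will need it for planning.

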### 2.12. Qualitative Data Analysis

For qualitative data, parent interviews will be audio-recorded and transcribed verbatim, and transcripts will be analyzed. A two-stage process will be followed to analyze interview transcripts. The first interview transcript will be pilot coded independently by two researchers to agree on a coding strategy (i.e., to ensure both researchers are coding consistently and to discuss and resolve any difficulties). Initial findings of the pilot transcript will be discussed before the researchers independently code the remaining transcripts. This will involve reading and re-reading transcripts, coding the content into themes and sub-themes and mapping these, with supporting direct quotes. The sample size for interviews will be determined based on data saturation.

## 3. Discussion

This study will examine the efficacy of Healthy Habits Triple P, an online intervention developed to improve children’s snacking and mealtime behaviours and related parenting practices. Healthy Habits Triple P has been developed in response to research identifying parents as important for behaviour maintenance and behaviour change in relation to their children’s snacking and mealtime behaviours [49]. Interventions that aim to alter the child’s eating behaviours often focus on parents as a proximal influence [50]. Prior interventions have varied in content, such as programs that seek to increase parental awareness of their child’s obesity risk [51], encouraging regular family routines around mealtimes, sleep, and/or media use [52], and family-based obesity prevention strategies that seek to engage the whole family unit [53] or intervention approaches that focus more directly on parents’ own weight management and nutrition [54].

Online administered, preventive public health interventions addressing lifestyle-associated disease risk factors could be cost-effective and could easily be scaled up. A recent systematic review by Gomes et al. (2020) evaluated the effectiveness of web-based interventions in changing parental feeding practices [23]. The review demonstrates that several intervention elements that are central to social cognitive theory, such as ‘*goals and planning*’ and ‘*feedback and monitoring*’, have been infrequently incorporated into interventions to date [26]. There is also evidence that healthy eating and physical activity interventions that combine self-monitoring with at least one other self-regulatory strategy tend to be more effective than programs that do not include these elements [55]. Healthy Habits Triple P builds upon previous research in this area by incorporating important drivers of behaviour change, including ‘goal setting’, ‘monitoring of parent and child behaviour’ and parent ‘self-reflection’. It aims to develop parents’ capacity for self-regulation as a central skill, resulting in parents becoming independent problem solvers and being able to implement parenting strategies effectively.

The systematic review by Gomes et al. (2020) also found that most parent-focused web-based interventions did not improve diet-related parenting practices, except for food availability [23]. These negligible effects could be attributed to the inclusion of active control groups which, in many studies, received content that was overly similar to that provided to the intervention groups. In our trial, a waitlist control group will be used to maximize treatment separation and help prevent the problem of diluted effect, reported in previous studies.

It is important for parent-focused interventions: to acknowledge that each child has different choices and behaviours related to eating; to address parents’ own beliefs, attitudes and goals related to healthy eating; and to promote strategies to address other family factors, such as involving other caregivers [56]. Our intervention tailors to individual circumstances by helping parents to have realistic expectations of their child and themselves, given their child’s age and stage of development; to develop child-focused goals that are based on their own individual needs and priorities; and to develop and maintain effective daily routines by planning ahead and involving other family members.

One potential limitation of the study is the reliance on parent-reported measures for outcome assessment. However, at minimum, the results from this study will provide a good indication of whether an intervention such as this is practical to deliver and acceptable to parents. Future studies should explore the concordance of parent-reported parenting and child behaviour outcomes with observed measures of parent and child behaviour. This study provides the opportunity to estimate important study-specific parameters required to inform the design of future definitive controlled trials [57] which, if successful, will pave the way toward implementation as a preventive public health intervention within existing healthcare settings.

## Data Availability

Not applicable.
